### Additional screening measures

The following measures were used during screening to assess for participant eligibility.

#### Mobility impairment

Experiencing mobility impairment is determined by endorsing “mild”, “moderate”, “severe”, or “extreme or cannot do” on at least one item on the WHODAS 2.0 (described above) 5-item “Getting Around” subscale, or “Yes” on at least one item of items 1–6 of the *Adapted Brief Disability Questionnaire* (BDQ) [84] The BDQ is used to assess whether activities were limited due to health in the prior week (e.g., climbing upstairs or walking uphill). Items are scored on a 3-point scale from 1 (No, not at all) to 3 (Yes, moderately or definitely).

#### Cognitive impairment

The *Montreal Cognitive Assessment* (MoCA) was designed to rapidly detect mild cognitive impairment [86]. Participants complete a variety of tasks that assess attention, memory, executive functioning, language, visuoconstructional skills, and orientation. Scores of these tasks are summed to produce a single score. Scores range between 0 and 30, with scores 26 or above considered normal. More recent research has indicated that a lower cut-off of 25 is optimal for detecting no cognitive impairment [128, 129]. Therefore, a cut-off of 25 was used in the current study to increase the specificity. Participants will be assessed for cognitive impairment remotely using the Full MoCA via Zoom when possible; if participants do not have access to Zoom, the telephone MoCA will be administered [130]. Participants must receive a score of 25 or above to be eligible to participate in the study.

##### Sleep and circadian functioning

The PROMIS-SD has been described above and will also be used as a screening measure to determine if participants exhibit a sleep or circadian disturbance. Participants who select 4 (quite a bit) or 5 (very much) on one or more items will be eligible to participate in the study.

#### Sleep disorders

The *Structured Clinical Interview for Sleep Disorders* (SCISD) is an interview designed to detect the presence of sleep and circadian diagnoses according to the DSM-5 [89]. For screening, the present study included the following diagnoses to be assessed by the SCISD: hypersomnolence disorder, obstructive sleep apnea hypopnea syndrome, REM sleep behavior disorder, and narcolepsy. The presence of REM sleep behavior disorder and narcolepsy is an exclusion criterion for the study as they cannot be addressed by TranS-C. The SCISD will also be used to collect diagnostic information pertaining to the presence of the following sleep disorders at pre-treatment: insomnia, circadian rhythm sleep–wake disorders, restless leg syndrome, nightmare disorder, and non-REM sleep arousal disorder: sleepwalking and sleep terror types.

### Therapist exploratory measures

#### Adherence

The *Therapist Adherence Rating Scale* (TARS) is a 5-item scale used by therapists to rate a client’s treatment adherence [134]. This scale will be completed at the end of each treatment session. Each item was rated on a scale from 0 to 100% with 10% increments. A total score will be calculated by averaging all five items, across all eight sessions to produce a single score.

#### Acceptability, appropriateness, and feasibility

Therapists will rate the acceptability, appropriateness, and feasibility of their version of TranS-C using the following 4-item measures: *Acceptability of Intervention Measure* (AIM), *Appropriateness of Intervention Measure* (IAM), and *Feasibility of Intervention Measure* (FIM) [135]. This scale will be completed at the end of each treatment session. All three measures are rated on a 5-point scale from 1 (completely disagree) to 5 (completely agree). A total score will be calculated for AIM, IAM, and FIM by averaging all four items and across all eight sessions.

### Therapist fidelity measures

#### Memory support

The *Memory Support Rating Scale* (MSRS) is a reliable and valid observer-coded measure that assesses the frequency and type of memory support used by treatment providers by analyzing treatment session video recordings [121]. MSRS coders are independent of the treatment provider and assessment teams and are masked to treatment condition. Coders will rate one randomly selected treatment session for each participant. Two measures are derived: the amount of memory support used per session and the number of different types of memory support strategies used per session.

The *Memory Support Treatment Provider Checklist* is a provider-rated measure of the use of the four memory support strategies that comprise the Memory Support Intervention for this study: Application, Categorization, Cue-based Reminder, and Evaluation. Therapists will rate the extent to which they delivered each memory support strategy in a given session on a 4-point scale: never (0 times), a few (1–2 times), often (3–5 times), and many (6 + times). These responses will be scored as never (0 times) = 0, a few (1–2 times) = 1, often (3–5 times) = 2, and many (6 + times) = 3. Two additional variables will be calculated: the total number of times memory support was utilized by summing the scores for each type of memory support on the scale (total number of memory supports used) and the total number of distinct memory support categories used out of a maximum possible total of four (total number of categories of memory support used). As the items on the scale are a range (e.g., 3–4 times), the total number of memory supports used represents a general estimate of memory support used, rather than a precise estimate. Therapists delivering MSI will complete this measure after each treatment session.

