### *TranS-C* + *Memory Support*

The TranS-C + MSI condition is identical to the TranS-C alone condition with the exception that Memory Supports will be integrated without adding to the length of the session. Therapists in this condition will be trained to administer an average of 10–12 instances of constructive memory support per session. The rationale is that in our prior research, the optimal dose in which 75% of patients reached a clinically meaningful change ranged from 8 to 12. This dosage of 10–12 is meant as a conservative goal, given that the majority of outcomes were maximized with fewer than 10 memory supports per session [9].

The streamlined MSI used in this study is comprised of 4 constructive memory support strategies: evaluation, categorization, cue-based reminder, and application. Evaluation involves patients evaluating the benefits and drawbacks of a treatment point or comparing the point to an alternative, which promotes deeper processing and conceptual understanding [102, 103]. Categorization is where the participant groups information by higher-order categories, which has been shown to improve recall [104, 105] and increase memory capacity [106, 107]. Cue-based reminders encourage participants to utilize internal and external cues that increase the potential for transfer of knowledge from therapy to everyday life [108]. Application encourages participants to apply learned material in therapy to similar situations [109, 110].

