### Fidelity checks

To assess therapist competence and fidelity to treatment, data from the Provider-Rated TranS-C Checklist, checklist of treatment elements specific to TranS-C, and the Memory Support Treatment Provider Checklist will be reported. The Memory Support Treatment Provider Checklist will be used to evaluate whether providers delivered the recommended dose of memory support.

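### The provider checklist labels a sum of 0–3 band codes as a number of memory supports; a session on the 10–12 target scores at most 8, so the sum cannot serve as the dose count

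*Protocol article*

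**What the plan says.** The section on TranS-C + Memory Support states the dose as a count. Therapists are trained to deliver "an average of 10–12 instances of constructive memory support per session".

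The Memory support section, under Therapist fidelity measures, describes the Memory Support Treatment Provider Checklist as "a provider-rated measure of the use of the four memory support strategies that comprise the Memory Support Intervention for this study". Each strategy gets one of four frequency bands: "These responses will be scored as never (0 times) = 0, a few (1–2 times) = 1, often (3–5 times) = 2", "and many (6 + times) = 3". Two further variables are then built. One is the number of distinct strategies used, out of four. The other is "the total number of times memory support was utilized by summing the scores for each type of memory support on the scale", also labelled as the total number of supports used. A caveat follows: because the items are ranges, "the total number of memory supports used represents a general estimate of memory support used, rather than a precise estimate".

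Fidelity checks then says: "The Memory Support Treatment Provider Checklist will be used to evaluate whether providers delivered the recommended dose of memory support". It gives no conversion from codes to counts and no threshold on the 0–12 scale.

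A separate measure, the MSRS, is coded from session recordings by masked coders: "Coders will rate one randomly selected treatment session for each participant". The Manipulation check section uses it to compare the arms on the amount and number of types of constructive memory support.

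**The concern.** The target is in instances per session, while the checklist total is a sum of ordinal codes carrying the name of a count. Both happen to end at 12, which invites a direct comparison that is not valid.

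The caveat about a general estimate does not cover this. It describes imprecision around a count because each band is a range. The problem here is a scale that never errs upward and always errs downward at the doses of interest.

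Dose matters to how this trial will be read. The Background suggests that the amount delivered in the previous trial may have been too small, and the Discussion lists the increased dose among the study's contributions. A fidelity report that set the code sum beside 10–12 would describe adherent therapists as falling short.

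**Working it through.** **Inputs.** Four strategies; codes 0 for 0 times, 1 for 1–2, 2 for 3–5 and 3 for 6 or more (Memory support); target 10–12 instances per session (TranS-C + Memory Support). The plan states no figure of its own to reproduce.

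**Step 1: code against count for one strategy.** The code equals the count at 0 and 1 and is smaller from 2 upward. The sum over four strategies therefore equals the true count only when every strategy is used zero times or once, that is, at no more than 4 supports. With 5 or more supports it is always too low.

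**Step 2: smallest count that yields a given score.** Within a strategy, codes 1, 2 and 3 need at least 1, 3 and 6 instances, so the successive points cost 1, 2 and 3 instances. Since the cost rises, the cheapest route takes the first point in all four strategies (4 × 1 = 4), then the second in all four (4 × 2 = 8, running total 12), then the third (4 × 3 = 12, running total 24).

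| Score | Minimum instances | Example split |
|---|---|---|
| 7 | 4 + 3 × 2 = 10 | 3, 3, 3, 1 |
| 8 | 4 + 4 × 2 = 12 | 3, 3, 3, 3 |
| 9 | 12 + 1 × 3 = 15 | 6, 3, 3, 3 |
| 10 | 12 + 2 × 3 = 18 | 6, 6, 3, 3 |
| 11 | 12 + 3 × 3 = 21 | 6, 6, 6, 3 |
| 12 | 12 + 4 × 3 = 24 | 6, 6, 6, 6 |

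A score of 7 already proves at least 10 supports, 8 at least 12 and 9 at least 15. All three lie below 10 when read as counts.

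**Step 3: score range at the target.** The lowest score arises when all supports fall in one strategy (code 3). Enumerating all splits gives:

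| True instances | Lowest sum | Highest sum |
|---|---|---|
| 10 | 3 | 7 |
| 11 | 3 | 7 |
| 12 | 3 | 8 |

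**Step 4: averaging does not help.** The target is an average, so the same check was made over eight sessions. A mean of 10, 11 or 12 instances allows a mean score of at most 7.0, 7.5 or 8.0. This follows from Step 2: between scores 4 and 8 each point costs 2 instances, so the ceiling is 4 + (mean − 4)/2.

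**Step 5: the sum does not rank sessions by amount.** A split of 3, 3, 3, 1 is 10 supports and scores 2 + 2 + 2 + 1 = 7. A split of 6, 6, 0, 0 is 12 supports and scores 3 + 3 = 6.

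**Step 6: what the bands can support.** Replacing each band by its lower limit (0, 1, 3, 6) gives totals of 6–10, 6–11 and 6–12 for 10, 11 and 12 true instances, so an on-target session can register as on target. Upper limits exist only when no strategy is rated 6 or more. Even then the interval is wide: codes 2, 2, 2, 1 mean 3 + 3 + 3 + 1 = 10 to 5 + 5 + 5 + 2 = 17 supports, and codes 2, 2, 1, 1 mean 8 to 14.

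**The case against.** The strongest reply is that Fidelity checks names the instrument and not the summed variable. The totals are described as additional variables, so the item-level bands are recorded too and could be set against 10–12 directly. The article is also a condensed document, and a conversion rule may stand in a fuller one. This reply holds to the extent that nothing shown says the sum will be compared with 10–12. A reader might infer that adherent therapists are bound to be reported as below target; the text does not support that as a certainty. What remains is that the sum is the only amount variable the article derives from the checklist, it is named as a count, and the checklist is the tool assigned to the dose check.

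A reader might also infer that a null result would be put down to under-dosing, or a positive one credited to the wrong dose. The documents do not support that either. The manipulation check uses the MSRS, which does not rely on the 0–3 codes and gives a recording-based measure of amount in both arms. None of the Aim 1, 2 or 3 analyses is stated to use the checklist. This point stands and limits the consequence to the fidelity report.

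Finally, a better use of the checklist still gives wide bounds that will often not settle whether 10–12 was met. That is true, and it is a reason to report the MSRS amount beside it.

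**Conclusion.** The scoring rule is wrong as written: it gives the name of a count to a quantity that is not one. At the target dose the understatement is at least 3 (10 − 7) for 10 instances and at least 4 (11 − 7 and 12 − 8) for 11 or 12, and it is larger when supports are concentrated in fewer strategies. These figures are exact and rest only on the stated bands and codes, with therapists rating their own counts correctly.

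The practical effect, on-target sessions appearing under-dosed, is conditional on the sum being read as labelled. The effect is confined to a descriptive fidelity measure. Treatment-effect estimates, error rates, power and the MSRS manipulation check are untouched. It should be corrected because the dose check bears on interpretation and the correction is cheap, but it does not threaten the trial's main conclusions.

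**What to change.** 1. Rename the 0–12 sum an intensity score and state that it is not to be compared with the 10–12 target.
2. For the dose check, convert each band to its count range (0, 1–2, 3–5, 6 or more). Report the lower-bound total per session, with an upper bound only for sessions in which no strategy is rated 6 or more.
3. Alongside it, report the MSRS amount of constructive memory support per session in the TranS-C + MSI arm against 10–12. The planned manipulation check compares arms, and this adds a comparison with the target.

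The cost is scoring and wording only. The bands are already recorded and the MSRS coding is already planned. Trial status gives recruitment through October 2026, so on this document collection is still under way and the rule can be set before analysis. The downside is that neither source is complete: the checklist covers every session but with wide bounds, and the MSRS counts supports but in one randomly selected session per participant, so the average dose is estimated from a sample of sessions.

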#### Treatment content

The *Provider-Rated TranS-C Checklist* is a measure of TranS-C modules delivered during treatment [136]. The original 16-item checklist was adapted to include questions to assess the modules of TranS-C that were included in this study. These additional optional modules include reducing nightmares, tapering hypnotics, and problem solving for sleep challenges. At the end of each treatment session, the therapist will select which items on the list they delivered during that specific session. There is no limit to the number of items a therapist can select for each treatment session. Following previous research in the field [137], a checklist of treatment elements specific to TranS-C was devised. Each element will be rated for presence/absence (i.e., adherence) and quality of delivery (i.e., competence).

#### Treatment fidelity

Each treatment provider will be randomly allocated to deliver only one of the two treatments. The rationale for this decision is that, in prior studies, familiarity with memory supports has made it difficult for therapists to return to treatment-as-usual. Therapists will attend initial training workshops and annual workshops thereafter. In addition, therapists will use a treatment manual [59] and attend weekly supervision meetings. Weekly supervision will be conducted separately for therapists in each condition. Therapists allocated to the memory support condition will attend additional bi-monthly supervision to familiarize themselves with, and practice use of, the memory support strategies.

At the end of each treatment session, all therapists will complete the *Provider-Rated TranS-C checklist* to record the TranS-C modules they delivered [136]. Therapists in the TranS-C + MSI condition will also complete the *Memory Support Treatment Provider Checklist* to record the memory support that they delivered [138]. The *Memory Support Rating Scale* (MSRS) will be used to assess the frequency and type of memory support used by therapists by analyzing one randomly selected session per client [121]. All therapy sessions will be recorded, and a randomly selected subset (10% of sessions) will be closely scrutinized by blind judges using the checklist of treatment elements specific to TranS-C. Fidelity scoring is described in the planned analysis section below.

### Participant timeline {13}

See Table 2 for timing of study measures.

#### Sample size {14}

For Aim 1, sample size was determined by conducting a power analysis using Optimal Design [139, 140] for person-randomized, repeated measures trials with four timepoints (pre-treatment, post-treatment, 6FU, and 12FU). Using a prior dataset comparing CT + MSI and CT-as-usual for depression [25] (R01MH108657), the effect size was calculated for midlife and older adults (≥ 50 years) by averaging the effect size for depression severity at post and 6FU. This approach yielded an effect size of* d* = 0.50. To achieve 80% power, 146 participants are needed. Adding 20% for attrition results in a sample size of 176. For Aim 2, Fritz and MacKinnon [141] provide recommendations for mediation sample size. Using data from R01MH108657 for midlife and older adults (≥ 50 years), the path from the predictor (average constructive memory support) to the mediator (recall at mid-treatment) was small to medium (*f* = 0.18) and the path from the mediator (recall at mid-treatment) to outcome (functional impairment at post-treatment) was medium (*f* = 0.23). Based on these estimates, a sample size of 148 is needed. Adding an additional 20% for attrition results in a sample of 178. The powerMediation package in R [142] was used to calculate the minimum detectable indirect effect of average constructive memory support on outcomes at 6FU and 12FU via recall at mid-treatment. With the proposed sample size of 178 needed for mediation at post-treatment, a minimum standardized indirect effect of 0.56 for outcomes at 6FU and 0.66 for outcomes at 12FU can be detected. The present study focused on powering the primary timepoint of interest, post-treatment. As treatment effects tend to decline over time, we may not be adequately powered to detect statistical significance at 6FU and 12FU. Thus, effect sizes, rather than statistical significance, will be emphasized for the follow-up timepoints. For Aim 3, a minimum detectable effect size difference was calculated via PowerUp! [143]. Estimates from pre-treatment to post-treatment impairment were generated from two prior datasets: (1) midlife and older adults (≥ 50 years), who were randomized to CT + MSI and CT-as-usual [25] (R01MH108657) and (2) midlife and older adults (≥ 50 years), who participated in the pilot trial of TranS-C + MSI [24]. The moderator with the smallest estimates (education from the R01MH108657 trial) was used to help ensure adequate sample size. With an alpha of 0.05, 80% power, and a sample size of 178 (calculated for Aim 2 mediation), the MDES for the moderator effect was *d* = 0.24. Considering that this effect size is comparable to the effect size yielded by similar analyses using prior data (*d* = 0.25 in the R01MH108657 trial), the sample size calculated for Aim 2 will be sufficient to power Aim 3. Together, a minimum sample size of 178 will be sufficient to power all three aims.

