### Trial design {8}

This study is a parallel group, randomized, controlled, superiority trial. Participants will be randomized to TranS-C + MSI or TranS-C alone with a 1:1 allocation ratio.

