## Statistical methods

An alpha = 0.05 will be used for each primary hypothesis. The Benjamini–Hochberg procedure [145] will be used to correct for multiple testing for confirmatory analyses on the primary outcomes (i.e., PROMIS-SD, SDS, SWLS).

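### The Aim 1 power figure is for one outcome and shows no allowance for the Benjamini-Hochberg correction over three primary outcomes; if computed at alpha 0.05, 80% is an upper bound on per-outcome power

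*Protocol article*

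**What the plan says.** The section Sample size {14} bases Aim 1 on Optimal Design for "person-randomized, repeated measures trials with four timepoints (pre-treatment, post-treatment, 6FU, and 12FU"). It uses one standardised effect of 0.50, taken from depression severity in an earlier trial among participants aged 50 or over. From this it concludes: "To achieve 80% power, 146 participants are needed". Attrition takes 146 to 176. The enrolment target of 178 comes from the Aim 2 mediation calculation, and the section ends: "Together, a minimum sample size of 178 will be sufficient to power all three aims".

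For Aim 1 the section gives no alpha, no number of tests and no definition of power. The only alpha printed there is 0.05, for Aim 3.

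The opening of Statistical methods says: "An alpha = 0.05 will be used for each primary hypothesis". It then says that the Benjamini-Hochberg procedure "will be used to correct for multiple testing for confirmatory analyses on the primary outcomes (i.e., PROMIS-SD, SDS, SWLS"). Table 1 assigns one of these three to each Aim 1 domain: sleep and circadian functioning, daytime functioning, and well-being.

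**The concern.** The power statement and the decision rule are both printed in this document, and they are not reconciled. A calculation with one effect size and no mention of multiplicity reads as power for one test at 0.05. The rule that will be applied is stricter: with three outcomes, Benjamini-Hochberg compares the ordered p-values with 0.0167, 0.0333 and 0.05.

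What is at stake is how a non-significant result on a single primary outcome, PROMIS-SD in particular, will be read. The gap is largest when benefit is confined to one outcome, and the protocol gives some reason to consider that case. Its Discussion notes that daytime functioning and well-being were not entry criteria, so participants who already score well there may have little room to improve. Sleep disturbance, by contrast, is an entry criterion.

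**Working it through.** **Inputs from the protocol.** d = 0.50, 80% power, 146 evaluable (Sample size {14}); 1:1 allocation, so 73 per arm (Trial design {8}); alpha 0.05 per primary hypothesis and Benjamini-Hochberg over three outcomes (Statistical methods).

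**Assumptions.** Tests are two-sided. Correlation among the three test statistics is 0 to 0.7 (the protocol gives none). Test statistics are approximately normal.

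**Step 1: try to reproduce 146.** The simple two-group formula gives N = 4 × ((1.960 + 0.842) / 0.50)² = 125.6, so 126 (128 with the t distribution). This is not 146. Optimal Design also needs within- and between-person variances, which are not printed, so the mismatch does not show that 146 is wrong. A repeated-measures formula that divides the simple N by the reliability of the person-level slope gives 146 at unadjusted 0.05 when that reliability is about 0.87 (127.5 / 146 = 0.87). Because the basis of 146 is unknown, two starting points are carried forward:

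- A: 146 gives exactly 80% at unadjusted 0.05. Non-centrality = 1.960 + 0.842 = 2.802.
- B: the simple two-group formula at 146. Non-centrality = 0.50 × √(73/2) = 3.021; unadjusted power = Φ(3.021 − 1.960) = Φ(1.061) = 85.6%.

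**Step 2: bounds that need no correlation.** Every Benjamini-Hochberg rejection has p ≤ 0.05, and every p ≤ 0.05/3 = 0.0167 (critical value 2.394) is rejected. Per-outcome power therefore lies between the Bonferroni value and the unadjusted value, whatever the other outcomes do:

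- A: from Φ(2.802 − 2.394) = Φ(0.408) = 65.8% up to 80%.
- B: from Φ(3.021 − 2.394) = Φ(0.627) = 73.5% up to 85.6%.

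**Step 3: simulation within those bounds.** 600,000 correlated normal triples per scenario, Benjamini-Hochberg at 0.05, ranges over correlation 0 to 0.7:

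| Scenario | A (80% unadjusted) | B (85.6% unadjusted) |
|---|---|---|
| Per outcome, three true effects | 76–78% | 83–84% |
| Per outcome, two true effects | 72–73% | 79–80% |
| Per outcome, one true effect | 66–67% | 74% |
| At least one primary significant, three true effects | 84–97% | 89–99% |
| At least one primary significant, one true effect | 67% | 75% |

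Under A the loss from 80% is 2–4 points with three true effects, 7–8 with two and 13–14 with one.

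**The case against.** The strongest reply is that nothing printed is shown to be wrong. A reader might infer from the missing allowance that the planned test fails to deliver 80% power, or that Aim 1 is underpowered. The documents do not support that, for three reasons.

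- **The alpha behind 146 is unknown.** With d = 0.50 and 73 per arm, 80% power corresponds to a two-sided alpha of about 0.029 (3.021 − 0.842 = 2.179). At 0.0333, the second Benjamini-Hochberg threshold, the simple formula gives 142–144. An allowance therefore cannot be ruled out. It cannot be inferred either, since 146 also fits an unadjusted repeated-measures calculation (Step 1).
- **The kind of power is not stated.** If 80% means at least one significant primary outcome, the trial exceeds it on both starting points when all three effects are real.
- **The Objectives expect benefit in all three domains.** Under that hypothesis the per-outcome loss is only 2–4 points on A, and B stays above 80%. The 66–67% figure needs both starting point A and benefit on one outcome alone.

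These arguments stand and make the conclusion conditional. They do not remove it. Alpha is set for each primary hypothesis, each domain has its own primary outcome and a single effect size was used, so per-outcome power is the natural reading. Even on B, power is about 74% if one outcome benefits.

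It may also be said that power inputs belong in the full protocol or analysis plan. That is fair for the variance components. The power figure, the sufficiency claim and the correction, however, are all stated here, and the first two take no visible account of the third.

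**Conclusion.** The point holds in conditional form. The Aim 1 calculation is for one outcome and shows no allowance for the Benjamini-Hochberg correction. If it was done at two-sided 0.05, the stated 80% is an upper bound on per-outcome power, which runs from 76–78% down to 66–67% as the number of outcomes that benefit falls from three to one. If the simple two-group figure of 85.6% is the better starting point, the range is 83–84% down to 74%.

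The size rests on the assumed correlation of 0 to 0.7 and on normal test statistics in place of the four-timepoint hierarchical model. The bounds in Step 2 do not depend on the correlation. It is not established that the trial misses 80%, nor that 146 is an arithmetic error. What is established is that the power figure, and the claim that 178 serves all three aims, are not tied to the test that will decide Aim 1.

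**What to change.** In Sample size {14}:

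1. State the alpha used for Aim 1, and whether the 80% is power per outcome or power for at least one primary outcome.
2. Either report power under Benjamini-Hochberg as a range by number of outcomes affected, with the assumed correlations, or label 80% as unadjusted power for a single outcome.
3. Reword the closing claim about all three aims to match.

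This takes a short simulation with the original Optimal Design inputs and a text edit. Enrolment stays at 178. The price is a slightly less favourable power figure in print.

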#### Aim 2: Patient memory as a mediator of treatment condition and sleep and circadian functioning

Structural equation modeling (SEM) will be used to test whether patient memory for treatment contents at mid-treatment (i.e., session 4) and post-treatment mediates the relationship between treatment condition (TranS-C + MSI versus TranS-C alone) and the primary patient outcome of sleep disturbance and the secondary patient outcome of sleep-related impairment (measured by the PROMIS-SD and PROMIS-SRI respectively). Three simple mediation models will be specified for each of the two sleep and circadian dysfunction measures at each timepoint (post-treatment, 6FU, 12FU). For each model, the indirect effect of treatment condition to treatment outcome via patient memory will be assessed.

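### The Aim 2 sample size of 148 does not follow from the stated path estimates, so the claim that 178 powers all three aims does not hold for Aim 2

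*Protocol article*

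**What the plan says.** All the figures are in the protocol article, section Sample size {14}. The article says that published sources "provide recommendations for mediation sample size" and takes two estimates from adults aged 50 or over in a prior trial. The path from average constructive memory support "to the mediator (recall at mid-treatment) was small to medium (*f* = 0.18"), and the path from recall at mid-treatment "to outcome (functional impairment at post-treatment) was medium (*f* = 0.23"). It continues: "Based on these estimates, a sample size of 148 is needed", and then "Adding an additional 20% for attrition results in a sample of 178". The section ends: "Together, a minimum sample size of 178 will be sufficient to power all three aims".

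The section gives 80% as the power target for Aims 1 and 3 but gives no target for Aim 2. It does not name the test of the indirect effect that lies behind 148. Statistical methods sets alpha at 0.05 for each primary hypothesis and does not state sidedness.

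The Aim 2 analysis section specifies simple mediation models in which treatment condition is the predictor, memory for treatment is the mediator, and PROMIS-SD and PROMIS-SRI are the outcomes: "For each model, the indirect effect of treatment condition to treatment outcome via patient memory will be assessed".

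**The concern.** An indirect effect is the product of two paths, and detecting it requires evidence on both. A sample that gives only moderate power on the weaker path cannot give 80% for the product under the usual tests. With f = 0.18 on the first path, 148 looks too small at sight.

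The stake is how Aim 2 will be read. It is the trial's test of its proposed mechanism, and the protocol names post-treatment as the time point of primary interest. If readers are told that the aim is adequately powered, a non-significant indirect effect can be taken as evidence against the memory mechanism when the design had little better than an even chance of detecting it at the stated effect sizes. The model that was powered is also not the model that will be fitted, so the article gives no power figure for the planned Aim 2 test at post-treatment.

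**Working it through.** **Inputs from the protocol (Sample size, Statistical methods).** Path a: f = 0.18. Path b: f = 0.23. N = 148 before attrition and 178 after. Alpha 0.05.

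**Assumptions.** Two-sided alpha; 80% power for Aim 2, as for Aims 1 and 3; f is Cohen's f, that is, a path coefficient with unit-variance predictor and residuals.

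**Step 1: the attrition step.** 148 × 1.20 = 177.6, so 178 follows from 148. If 20% of 178 are lost, 178 × 0.80 = 142.4, leaving 142 completers.

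**Step 2: power of each path.** Noncentral t with noncentrality f√N and N − 2 (path a) or N − 3 (path b) degrees of freedom. At N = 148, √148 = 12.17:
- path a: 0.18 × 12.17 = 2.19, power 58.5%
- path b: 0.23 × 12.17 = 2.80, power 79.4%

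**Step 3: power for the indirect effect.**
- Joint significance: the product of the two path powers. At 148, 0.585 × 0.794 = 46.5%.
- Sobel: SE = √[(0.18² + 0.23²)/N]. At 148, SE = 0.2921/12.17 = 0.0240. Then ab/SE = 0.0414/0.0240 = 1.72, and Φ(1.72 − 1.96) is about 41%.
- Bootstrap: Monte Carlo simulation of the three-variable model with no direct effect. The bias-corrected column gives the spread over separate runs of 1,000 to 4,000 replicates.

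| N | Path a | Path b | Joint significance | Bias-corrected bootstrap | Percentile bootstrap | Sobel |
|---|---|---|---|---|---|---|
| 142 | 56.8% | 77.7% | 44.1% | about 52–55% | about 40% | 39% |
| 148 | 58.5% | 79.4% | 46.5% | about 55–57% | about 43–44% | 41% |
| 178 | 66.6% | 86.3% | 57.4% | about 63–66% | about 55% | 47% |

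One-sided joint significance gives 61% at 148 and 71% at 178. No test reaches 80% at 148 or 178.

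**Step 4: N for 80% power (before attrition).** Bias-corrected bootstrap about 235–245 (79.5% at 235, 81.5% at 245); joint significance 266; percentile bootstrap just over 270 (79% at 270); Sobel 391. One-sided joint significance needs 215.

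**Step 5: where 148 does appear.**
- Path b alone, large-sample formula: (1.960 + 0.842)²/0.23² = 7.85/0.0529 = 148.4. This leaves out path a, which by the same formula needs 7.85/0.0324 = 242.
- Both paths at about 0.26: bias-corrected bootstrap power at 148 is about 82%. Both stated estimates are smaller than 0.26.
- Reading the printed f as f² gives N of 54 (joint significance) to 78 (Sobel), not 148.

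The protocol does not say which route was taken, so the origin of 148 remains a conjecture.

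**Step 6: the model powered against the model planned.**

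| | Sample size section | Aim 2 analysis section |
|---|---|---|
| Predictor | Average constructive memory support | Treatment condition |
| Mediator | Recall at mid-treatment | Memory at mid-treatment and post-treatment |
| Outcome | Functional impairment at post-treatment | PROMIS-SD and PROMIS-SRI |

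Predictor and outcome both differ. The powers above therefore test the stated calculation; they are not the power of the planned analysis.

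**The case against.** **The size depends on the test and on unstated conventions.** This is true. The Aim 2 power target and the sidedness are assumptions, and the Aim 2 hypothesis is directional. Two-sided power runs from 39% (Sobel, 142) to about 66% (bias-corrected bootstrap, 178), and a one-sided joint test gives 71% at 178. The size has to be quoted as a range, but no version reaches 80% or reproduces 148.

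**The calculation concerns a prior trial.** The present intervention is streamlined and aims at a higher dose of constructive support, so the true paths may be larger. That is possible, but the article presents 148 as following from the prior estimates, and it does not.

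**Aim 2 barely moved the sample size.** Aim 1 alone gives 176, so Aim 2 added two participants, and the multiplicity-corrected confirmatory tests are on PROMIS-SD, SDS and SWLS. This stands, and it limits the weight of the point.

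**Two stronger readings that the documents do not support.** First, a reader might infer that the plan overlooks low mediation power at follow-up, since it says that "a minimum standardized indirect effect of 0.56 for outcomes at 6FU and 0.66 for outcomes at 12FU can be detected". The same section goes on to concede that power at 6FU and 12FU may be inadequate and says that effect sizes will be emphasised there. A reader might also set 0.56 and 0.66 against 0.18 × 0.23 = 0.041 and call them many times too large. The inputs and scaling behind 0.56 and 0.66 are not given, and the 0.23 is a post-treatment path, so nothing shown puts the figures on a common scale. Second, a reader might infer that the whole trial is underpowered. The arithmetic here bears on Aim 2 only.

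**Conclusion.** The point holds for the post-treatment indirect effect. A sample of 148 does not follow from f = 0.18 and f = 0.23, and the closing claim of sufficiency is wrong for Aim 2. Under the assumptions stated in the working, power by joint significance and by bias-corrected bootstrap respectively is about 44% and 52–55% at 142 completers, 46% and 56% at 148, and 57% and 65% at 178 with no attrition. About 235 to 266 completers would be needed for 80% by those tests, and more by the less powerful ones. Because the calculation uses a different predictor and outcome from the planned models, the power of the planned Aim 2 test is unknown rather than equal to these figures. The power statements for Aims 1 and 3 are not shown to be wrong. This should be fixed; it is a correction to a mechanism aim and does not threaten the primary efficacy comparison.

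**What to change.** No additional enrolment is proposed. Change the text as follows:

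1. In the Sample size section, withdraw or correct the statement that 148 follows from the two path estimates.
2. Recompute Aim 2 at post-treatment for the planned model (condition to memory to PROMIS-SD and PROMIS-SRI), at the expected number of completers. Report either power or the minimum detectable indirect effect, and name the test, the sidedness and the power target.
3. Limit the closing sufficiency sentence so that it no longer covers Aim 2.
4. State in the Aim 2 analysis section that the indirect effect will be reported with its confidence interval, and that a null result at post-treatment is inconclusive and not evidence against mediation.

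The follow-up wording can stay as it is. The cost is one recalculation and a few sentences; the stated position on Aim 2 becomes less favourable, and the sample size, conduct and data collection do not change.
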